#### 2.1.3. Sample Size

To ensure that the size of the improvements realized by the intervention are of practical significance, we propose a minimum effect size of Cohen’s *d* = 0.3, which is a small-to-medium effect. A power calculation using this effect size and the proposed analysis plan (see below) was carried out using the program G*Power [35] and indicated that the minimum sample size we require for the study is n = 352. However, due to the difficult living conditions in the proposed recruitment areas (gang violence, long distances from residences to school centres, etc.), we expect a high dropout rate. Therefore, we propose to recruit a total of 480 children as this would allow for slightly more than 25% of the sample to stop participation in the study yet still allow us to maintain sufficient statistical power to detect the target effect size. Furthermore, the figure of 480 represents approximately one-third of 5th grade students attending Fe y Alegría Guatemala across their 46 centres. Thus, we would only need consent from one in every three children to achieve the necessary sample size. This sample size could be reduced if research teams were prepared to look for larger effect sizes. Furthermore, once this protocol is implemented, research groups should consider creating a contingency plan based on the specific conditions they encounter to address potential difficulties in recruitment.

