### 2.3. Instruments

#### 2.3.1. Comprehensive Assessment Battery

To obtain the baseline data of the participants and evaluate their subsequent cognitive and emotional performance after the intervention, we will use a battery of neuropsychological tests to assess the cognitive domains of language [36,37,38]: attention [39], executive functions [40,41,42,43,44], and social cognition [45]. We will also assess their mental health [46,47], emotional management [48], and quality of life [49]. Lastly, we will take measurements of their family’s socioeconomic level, clinical history, food consumption [50], exposure to violence [51], and academic performance (for detailed explanations of the assessment instruments, see Supplementary Materials). In total, there will be four assessment sessions, each lasting between 45 and 60 min. The session plan has been designed in a modular way that allows for flexible administration in order to accommodate participants who cannot attend the educational centre on a daily basis. Each module can be assessed in any order, and they can be applied one after the other within the same session (providing breaks in between), although assessing each module on different days would be ideal. Given the large number of tests that will be required for a comprehensive assessment, it will become difficult to compare results across tests. For this reason, converting results to percentiles or z-scores will need to be performed in order to make meaningful comparisons between instruments.

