Pre/post-evaluation data are best analyzed using an ANCOVA design in which post-scores are the dependent variable, and pre-scores serve as the covariate [63]. This will be conducted separately for each intervention, with the data collected at T2 serving as post-data for intervention 1 and pre-intervention baseline data for intervention 2. If desired, the effects of the two interventions can be directly compared by implementing a repeated measures ANCOVA. Given that it is likely that raw scores will be converted to and analyzed as percentile scores, normal distributions of the dependent variables may not be present. Accordingly, Bootstrapping or non-normal distributions in the Generalized Linear Framework should be considered to accommodate these data. Other covariates, such as sex, age, mean educational level of parents, etc., can be included in the analyses. It will also be possible to perform analyses for different subgroups of participants, either using multilevel, stratified models, or by separating out the subgroups, depending on the specific nature of the subgroups. In particular, we will explore the differences between the “normative” group (participants between the ages of 10 and 12, without any clinical diagnosis and with scores over the inclusion limit in the screening assessment tasks), and the “non-normative” group (participants 13 years old and above, having any clinical diagnosis, or with scores under the screening tasks limit). This last separation will be performed to explore the impact the program may have on children with additional difficulties. We will perform another ANCOVA analysis to explore the long-term changes in the participants at the end of the program (second block), considering the changes they might have experienced on the first block. Where multiple comparisons are undertaken due to the presence of many schools, age ranges, or other factors, appropriate corrections will be applied to the statistical tests. 

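### The percentile scale the plan expects to analyse shrinks change in low scorers and can distort the normative versus non-normative comparison; raw or z-scores should be named as the ANCOVA scale

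*Protocol article*

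**What the plan says.** Two sections of the protocol article deal with the outcome scale. Section 2.3.1 says that, to compare instruments, "converting results to percentiles or z-scores will need to be performed", and does not choose between the two. Section 2.5 leans one way: it calls it likely that "raw scores will be converted to and analyzed as percentile scores". It then says that normal distributions may not be present for that reason, and suggests bootstrapping or non-normal generalized linear models. The main analysis is an ANCOVA of the post-score on group with the pre-score as covariate.

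Section 2.5 also plans to explore differences between a normative group and a non-normative group. The latter includes children under the screening limit, which Section 2.1.1 sets at the 5th percentile for reading and non-verbal intelligence. The Introduction reports that disadvantage lowers cognitive performance in this population, but gives no mean or SD against any norm.

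The sample size is set in SD units: "we propose a minimum effect size of Cohen’s *d* = 0.3, which is a small-to-medium effect", from which "the minimum sample size we require for the study is n = 352".

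**The concern.** The article attributes the expected non-normality to its own rescaling and then proposes methods to work around it, although a scale without that effect is already named in Section 2.3.1.

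The percentile is a non-linear function of the score, steep in the middle and flat in the tails. The same gain on the test counts for less when a child starts low. Two things are at stake. First, a comparison of benefit between low-scoring and other children can show a difference that comes from the scale alone. Second, if the sample lies well below the norms, the ANCOVA loses information, and the sample size makes no allowance for this.

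**Working it through.** **Inputs.** From the article: d = 0.3, n = 352, 480 recruited, close to 1:1 allocation, ANCOVA with the pre-score as covariate. Assumed because the article does not state them: two-sided alpha 0.05, 80% power, T1–T2 correlation 0.6 or 0.7, and the distance of the sample mean below the norm mean. All figures treat children as independent; allocation by class is a separate matter.

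**1. The plan's own figure.** Per arm, 2(1.960 + 0.842)²/0.3² = 174.4, rounded up to 175. The exact noncentral t gives 176 per arm, 352 in total, with power 0.801. An ANCOVA calculation with f = 0.15 and one covariate gives 351, or 352 with equal arms. So 352 reproduces as a normal-theory figure. The dropout allowance is 1 − 352/480 = 26.7%.

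**2. Compression.** For a child at norm z-score z, a gain of 0.3 SD is worth 100 × [Φ(z + 0.3) − Φ(z)] percentile points.

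| Starting percentile | Gain in points |
|---|---|
| 50th (z = 0) | 11.8 |
| 16th (z = −1) | 8.3 |
| 7th (z = −1.5) | 4.8 |
| 5th (z = −1.645) | 3.9 |
| 2nd (z = −2) | 2.2 |

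**3. Subgroup comparison.** Suppose, for illustration, that one group starts at the 50th percentile and the other at the 5th, and that both gain 0.3 SD. The percentile analysis shows 11.8 against 3.9 points, a difference of 7.9 points with no true difference in SD benefit. Bootstrapping changes the standard error or interval, not the quantity estimated, so it leaves this difference in place.

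**4. Information in the ANCOVA.** Normal scores were simulated at 176 per arm, with percentile = 100Φ(z), rounded and held within 1–99. Information is the squared test statistic on percentiles relative to z-scores. The equivalent n is 352 × ratio.

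| Sample mean | Ratio | Equivalent n | Power at that n, d = 0.3 |
|---|---|---|---|
| At the norm | 0.92 | 324 | 0.77 |
| −1 SD | 0.82 | 289 | 0.72 |
| −1.5 SD | 0.70 | 246 | 0.65 |

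**5. What this means for power depends on the units of d.**

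- *d = 0.3 in residual-SD units.* The z-score ANCOVA then has 80% power, and the last column above applies. Direct simulation at correlation 0.6 gave 0.77, 0.73 and 0.66.
- *d = 0.3 in raw-SD units, correlation 0.7.* The effective d is 0.3/√(1 − 0.49) = 0.42 and z-score power is about 97%. Percentile power is about 96% at the norm, 93–95% at −1 SD and 90% at −1.5 SD. At correlation 0.6, z-score power is 94% and percentile power 92%, 89% and 84%.

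**6. Non-normal raw scores** (residual-SD d, correlation 0.6; z-score against percentile power).

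| Raw scores | Mean at norm | Mean −1 SD |
|---|---|---|
| Heavy-tailed | 0.78 vs 0.90 | 0.79 vs 0.82 |
| Right-skewed | 0.78 vs 0.88 | 0.78 vs 0.60 |

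Percentiles can therefore gain power near the norm, and can lose more than in the normal case below it.

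**The case against.** The strongest reply is that nothing is fixed. Percentiles are only called likely, z-scores are already permitted, and a final outcome scale is often settled in an analysis plan that is not shown. It is true that this is not a firm decision. But Section 2.5 states an expected scale and builds its choice of methods on it, so the point concerns a stated preference and not a missing detail.

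A reader might infer that the trial will be underpowered. The documents do not support that. The article does not say whether d = 0.3 is in raw-SD or residual-SD units, and under the raw-SD reading power stays above 80% in every normal-score scenario down to −1.5 SD. Nor does it say how far these children lie from the norms. The Introduction mentions earlier work on assessment scores for Guatemalan children; if the norms fit, the cost is only a few points of power.

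A reader might also infer that z-scores keep the power for free. They do not: a linear z-score carries over any skew, floor or outliers in the raw test, and step 6 shows cases where percentiles do better.

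It can be said, too, that Cohen's d is unit-free and can be computed on percentiles. That is correct, but it would be a different d from the one on the test's own scale. A non-normal model is not a clear remedy either: a fractional logit on percentiles recovered almost nothing in a check.

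None of this removes the compression in low scorers or its effect on the subgroup comparison.

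**Conclusion.** The point holds in limited form. The expected percentile scale is a poor default for this trial because it makes an equal SD gain look smaller in low scorers (about 12 points from the 50th percentile, about 4 from the 5th), and the plan intends to compare groups that are likely to differ in starting level. This follows from the transform and needs no assumption about power.

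The power cost is conditional. For roughly normal scores it is an information loss of about 8%, 18% or 30% at assumed sample means of 0, −1 or −1.5 SD. Whether that takes power below 80% depends on the units of d, the T1–T2 correlation, the fit of the norms and the shape of the raw scores, none of which the article gives. The change is worth making because it is easy, not because the trial is shown to fail without it.

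**What to change.** In Sections 2.3.1 and 2.5, name raw scores or z-scores as the ANCOVA scale. For z-scores, use one fixed reference per test, taken at T1 (for example the pooled T1 mean and SD), and apply it unchanged at T1, T2 and T3. Include age as a covariate; Section 2.5 already lists it as an option. Z-scores also meet the aim in Section 2.3.1 of comparing instruments.

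Use percentiles only for screening and for descriptive tables. Make the normative versus non-normative comparison on the same raw or z-score scale. Keep the bootstrap, resampling whole classes, as a sensitivity analysis for tests that prove skewed or heavy-tailed.

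The cost is a change of wording: raw scores must exist before any conversion, and percentiles can still be reported. The small downside is that linear z-scores keep any skew, floor or outliers in the raw scores, which is what the sensitivity analysis is for.

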Since all children will receive the intervention, we want to explore the effects this program may have on the children who do not meet the inclusion criteria but usually have special educational needs. Due to the nature of the intervention, it is impossible to implement it in a manner that allows both participants and the personnel administering the intervention to participate blindly. However, the personnel from the research team assessing the data will be blinded to group assignment to ensure as much of an unbiased outcome as possible. The interpretation of the data will also have to consider the group assignment to conclude the efficacy of the program.

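### The plan aims to compare normative with non-normative children, but its wording points to separate analyses and names no condition-by-subgroup term, so the comparison itself would go untested

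*Protocol article*

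**What the plan says.** All of this is in the protocol article. Section 2.5 sets the main analysis as an ANCOVA of the post-score on condition, with the pre-score as covariate. For subgroups it allows either multilevel, stratified models "or by separating out the subgroups, depending on the specific nature of the subgroups".

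It then singles out one pair. Normative children are aged 10 to 12, have no clinical diagnosis and score above the screening limits. Non-normative children are 13 or older, have any diagnosis, or score below those limits. The stated intention is to explore how the two groups differ, and the text adds: "This last separation will be performed to explore the impact the program may have on children with additional difficulties". Later in the section the aim is put again: "we want to explore the effects this program may have on the children who do not meet the inclusion criteria".

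No condition-by-subgroup term is named, and the size of the non-normative group is not given. The only power calculation, in section 2.1.3, is for the whole sample: d = "0.3, which is a small-to-medium effect", and the "minimum sample size we require for the study is n = 352".

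**The concern.** A question about differences between groups is a question about two effects at once: is the programme effect the same in both? A separate ANCOVA in each group tests something else, namely whether the effect in that group is zero. Neither test has equality of effects as its null hypothesis.

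The two questions come apart most when the groups differ in size. If the non-normative group is the smaller one, its test has less power, and a benefit equal to that of the other children can easily be non-significant there and significant in the larger group. A reader who sees that pattern may conclude that the programme works for typical pupils but not for those with additional difficulties. These are children whom section 2.4 deliberately keeps in the intervention, and section 4 aims at adoption into the school curriculum, so such a conclusion would have consequences.

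**Working it through.** **Inputs**
- Effect size d = 0.3, minimum total 352, recruitment target 480: section 2.1.3.
- Allocation as close to 1:1 as possible, by whole class: section 2.4.
- Significance level and power are not stated. Two-sided 5% and 80% are assumed because they reproduce the plan's figure.
- The non-normative share q is not stated. The range 10% to 50% is assumed.
- Children are treated as independent. The figure of 352 is reproduced on that basis.

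**The plan's own figure.** An ANCOVA with f = d/2 = 0.15, two groups and one covariate reaches 80% power at 351 children, or 352 with equal arms (power 80.1%). The figure of 352 is reproduced.

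**Separate tests when the effects are equal.** In a subgroup of n children split 1:1, power comes from the noncentral t with noncentrality d × √(n/4). With non-overlapping groups, the chance of a significant result in normative children and a non-significant one in non-normative children is

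power(normative) × [1 − power(non-normative)].

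Example, N = 352 and q = 20% (70 and 282 children): 0.709 × (1 − 0.236) = 0.542.

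| Share q | Non-normative n (of 352) | Power, non-normative | Power, normative | Misleading pattern, N = 352 | Misleading pattern, N = 480 |
|---|---|---|---|---|---|
| 10% | 35 | 14% | 76% | 65% | 72% |
| 20% | 70 | 24% | 71% | 54% | 58% |
| 30% | 106 | 33% | 65% | 43% | 44% |
| 40% | 141 | 42% | 58% | 34% | 33% |
| 50% | 176 | 51% | 51% | 25% | 23% |

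The true effects are identical in every row. A valid 5% test of equal effects would declare a difference 5% of the time.

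**When is the non-normative result more likely non-significant than significant?** Power is about 50% where d × √(n/4) = 1.96, so n = 4 × (1.96/0.3)² ≈ 171. That is 49% of 352 or 36% of 480.

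**Sensitivity to baseline adjustment.** If d = 0.3 is on the unadjusted SD and the pre-post correlation is r (assumed), the effective d is 0.3/√(1 − r²): 0.346 for r = 0.5 and 0.420 for r = 0.7. The threshold of 171 falls to about 128 or 87 children. The misleading pattern does not go away, because power rises in the larger group too. At N = 352 and shares of 10%, 20% and 30% it is 72%, 58% and 45% for r = 0.5, and 74%, 55% and 39% for r = 0.7.

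**What the interaction can deliver.** In SD units the standard error of the difference between the two effects is √(4/n₁ + 4/n₂). At N = 352:

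| Share q | SE | 95% CI half-width | Power for a 0.3 SD difference |
|---|---|---|---|
| 10% | 0.355 | 0.70 | 13% |
| 20% | 0.267 | 0.52 | 20% |
| 30% | 0.233 | 0.46 | 25% |
| 50% | 0.213 | 0.42 | 29% |

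The interaction addresses the right question, but with little precision. Correlation within classes would lower subgroup power further; it is not quantified here.

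**The case against.** A reader might infer that the plan fixes separate analyses as its method, or that it will take non-significance in the non-normative group as absence of benefit. The document supports neither. The sentence before the normative/non-normative comparison also offers multilevel, stratified models, and a multilevel model on all children could carry the interaction. The word separation may partly mean no more than sorting the children into two classes. No rule says how a non-significant subgroup result will be read, and the language throughout is exploratory.

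Three further points have force. One stated aim is the effect within children with additional difficulties, and for that a subgroup-specific estimate is the right target. The subgroup's size is unknown and could be large: it is a union of three criteria, and section 2.1.1 expects some children to be one or two years older than usual. Section 2.5 also describes these children as not meeting the inclusion criteria, so it is unclear whether all of them count within the 352 or 480. Finally, exact model terms for an exploratory analysis are often left to an analysis plan.

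These points limit the claim without removing it. The article does more than stay silent: it states a comparative aim, lists separation as a route, and uses that same word for this analysis. A stratified model does not by itself test a difference in effects either.

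**Conclusion.** The point holds in a limited form. The plan permits, and its wording leans towards, an analysis that does not answer the comparative question it sets. If results were then compared by significance, equal effects of d = 0.3 would look different 65% to 25% of the time at 352 analysed children, for non-normative shares of 10% to 50%. The misleading pattern is more likely than not at the 10% and 20% shares, but not at 30% or above. These figures assume two-sided 5% tests, 1:1 allocation, independent children and both groups counted within the 352.

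The analysis is exploratory and does not affect the main comparison. Severity is low to moderate.

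**What to change.** For any comparison of effects between the two groups, specify one model on all children: T2 score on T1 score, condition, subgroup and condition-by-subgroup, with the same class structure as the main analysis. Report the interaction estimate with its 95% CI beside each group's effect and CI from that model. Do not offer separate analyses as a way to compare effects; separate subgroup estimates may still be shown descriptively.

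Add two statements: no conclusion will be drawn from one group being significant and the other not, and a non-significant interaction will not be read as equal effect.

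The cost is one model term and a few sentences, with no new data. The drawback is that the wide interval will show how little this trial can say about a difference in effect.

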## 3. Discussion

This study protocol focuses on improving the cognitive and emotional competence of students from especially vulnerable areas of Guatemala City and consequently aims to improve their academic performance and quality of life. In addition, as the participants are minors living in very adverse socioeconomic conditions, they will have the opportunity to learn how to use electronic devices that they would not normally have access to, such as tablets or virtual reality headsets. Given the recent situation with the COVID-19 pandemic, this knowledge can be beneficial for effectively facing the educational challenges that schools currently face after two years of non-regularized schooling. The program is ambitious in terms of the number of tests it proposes to include. Nevertheless, when replicating this study, each research group can choose to vary the number of tests based on their particular research goals and the specific conditions encountered within their sample, and as the intervention progresses.

There is a great educational gap among students caused by the wildly varied situations in their homes. The closure of schools due to the COVID-19 emergency has widened this gap, as most of these vulnerable students do not have access to computers or the internet in their family homes. In addition, the low level of education of their relatives and the fact that they tend to live in small and overcrowded houses have a significant impact on their academic performance. The introduction of tablets has the secondary benefit of making it possible to reduce the digital gap between households while strengthening the capacity for teaching teams to design distance and face-to-face mixed education methodologies that increase the skill levels of students, thus reducing the educational gap. An equitable education is fundamental for exercising rights and increasing opportunities in the long-term.

If the results of this proposed program successfully achieves the expected impact, it could make a big difference in the future of these children, providing them with a chance to develop their cognitive and social abilities to previously unachievable levels, balancing the playing field with other children of their age. This program has been created to be applied in similar low-level socioeconomic contexts, which means that it could become a reliable tool to help children in similar conditions around the world, as the literature suggests [27,29,30]. If the program is effective, there are plans to transfer the knowledge derived from the application of the comprehensive neuropsychological stimulation program in vulnerable areas of Guatemala to particularly disadvantaged contexts in Andalucía (Southern Spain), where 15 of its neighbourhoods are among the poorest in Spain, based on the most recent report of Urban Indicators (Urban Audit) published by the National Institute of Statistics [64].

